### Data collection

#### Clinical evaluation

Patients will be followed by a study physician daily until discharge, and all signs and symptoms recorded in the case report form. An ultrasound scan will be performed on day 6 of illness to detect signs of plasma leakage. Clinical management decisions will remain in the hands of the attending ward doctors. In the event that shock or any other serious complication develops, the patient will be transferred to the appropriate ICU. Details of all adverse events will be recorded on specific forms, together with an assessment as to whether the event is likely to be related to any treatment received, and all serious events will be reported promptly to the DSMB.

Quality of life will be measured by questionnaire and visual analogue scale daily.

Patients who are fit to discharge on or after study day 3 may be followed as an outpatient until study day 6. All patients will be asked for attend a follow-up visit for review after 4 weeks.

#### Laboratory evaluation

Haematocrit, platelet and total cholesterol measurements will be carried out daily or more frequently if clinically indicated. These tests will be repeated at the follow-up visit.

Renal and liver function tests, electrolytes and coagulation profiles, will be carried out at enrolment, 48 hours later, day 5 or 6 of illness and at the follow-up visit. If the ALT measured 48 hours after enrolment is greater than 250 U/l, the study drug will be discontinued. It should, however, be noted that hepatic dysfunction might be secondary to dengue infection and could be positively affected by statin therapy.

Conventional serological and virological tests will be used to confirm dengue infection and identify the infecting serotype. Plasma samples collected at daily intervals until discharge (and daily until day 6 if discharged before day 6) will be assessed for viraemia levels, NS1 levels, and concentrations of various pro- and anti-inflammatory cytokines (TNF-α, IFN-γ, IL-6, IL-10).

DNA will be extracted from residual blood samples and genotyped for genetic variants known to be associated with severe dengue, for example, *MICB* and *PLCE1*[22].

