### Statins

Statins are inhibitors of 3-hydroxy-3-methylglutaryl-coenzyme A (HMG-CoA) reductase. They were first used clinically in the late 1980s and quickly became established as an effective drug for both lipid lowering and mortality reduction in cardiovascular disease [4]. They are currently one of the most prescribed classes of drugs globally. Statins have an excellent safety profile [5]. The most common adverse effects are rises in the level of liver transaminases and myopathy. These effects are rare and appear to be dose-related [5,6]. More recent research has demonstrated that statins have additional beneficial effects. These pleiotropic effects include the restoration or improvement of endothelial cell function, an increased production of nitric oxide, and a reduction in the release of cytokines and acute phase proteins. These effects lead to a reduction of inflammation within the vessel wall [7,8]. Observational studies suggest that statin therapy may result in improved outcomes for a diverse range of conditions, including sepsis and pneumonia [9-13]. In addition, there are a number of on-going randomised clinical trials to assess the therapeutic efficacy of statins in sepsis and acute lung injury (NCT00528580, NCT00676897, NCT00979121).

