### Aims of the trial

Typically, severe vascular leakage and shock occur around the fifth day of illness in patients with dengue [20]. It is possible that initiation of statin therapy early in the course of the illness may prevent or favourably modulate these effects. As the proportion of patients who develop shock or other complications after presentation to hospital is low (approximately 5%), a large trial would be required to demonstrate a clinical benefit [2,21]. However, this study presents an opportunity to assess formally the safety of using statins in the treatment of this disease. In addition, such a study will also provide an opportunity to investigate the effect of statin usage on the immune response during dengue infection and to generate preliminary data for planning a Phase III trial in the future.

Although there is extensive experience of using statins as a lipid-lowering agent, and an increase in the amount of observational data from their use in critically ill patients, this will be the first study looking at the use of statins in dengue. We propose to investigate the effect of lovastatin for 5 days in adult dengue patients presenting in the first 72 hours of illness. The rational of a 5-day treatment course is to cover the transient ‘critical’ phase of infection when complications arise, which typically occurs around the fifth day of illness [3]. Our proposed treatment course will start on the second or third day of illness and continue to the seventh or eighth day of illness, which is into the recovery phase. As this is the first study investigating statin therapy in dengue with a particular focus on safety, we propose a dose-escalation study, investigating 40 mg lovastatin versus placebo with a safety review after recruitment of the first 30 patients. If this review is satisfactory, we will increase the lovastatin dose to 80 mg and conduct a further safety review after the next 30 patients.

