### Inclusion and exclusion criteria

All patients aged 18 or more presenting to the Hospital of Tropical Diseases, Ho Chi Minh City with a clinical suspicion of dengue, less than 72 hours of fever and a positive rapid test for dengue non-structural protein 1 (NS1) will be eligible for recruitment into the study. Exclusion criteria are: signs or symptoms suggestive of another acute infectious disease, alanine transaminase levels greater than 150 U/l, creatine kinase levels greater than 1000 U/l, liver cirrhosis, myopathy, current or use within past week of statins, pregnancy and lactation. In addition, patients taking medications contraindicated for use with statins, for example, isoniazid for treatment of tuberculosis, will be excluded.

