### Secondary endpoints

The secondary endpoints of this study are fever clearance time (see definition), plasma viraemia (area under the log-transformed viraemia curve from enrolment until study day 6), platelet nadir between day 3 and 8 of illness, maximum haematocrit between day 3 and 8 of illness, percentage increase in haematocrit between day 3 and 8 of illness from baseline, maximum alanine transaminase (ALT) and creatine kinase (CK) recorded between day 3 and 8 of illness, lowest oxygen saturation recorded between day 3 and 8 of illness, number of patients in each group requiring colloid, and disease progression as defined by one or more of the following: (a) admission to the ICU, (b) diagnosis of shock (see definition), (c) diagnosis of severe bleeding (see definition), (d) development of encephalitis, (e) death. In addition, quality of life scores obtained using a visual analogue scale will be compared between treatment groups. The times from enrolment to the first sample with viraemia less than 1000 copies/ml and the first negative NS1 antigenaemia sample will be compared between treatment groups.

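### The listed blood schedule does not support peak ALT and CK over illness days 3 to 8: no ALT is listed on days 7–8, and the pre-dose value can count as the peak

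*Protocol article*

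**What the plan says.** The Secondary endpoints section of the protocol article lists "maximum alanine transaminase (ALT) and creatine kinase (CK) recorded between day 3 and 8 of illness". The Laboratory evaluation section sets out three groups of tests:

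- Daily: "Haematocrit, platelet and total cholesterol measurements will be carried out daily or more frequently if clinically indicated".
- At set times: "Renal and liver function tests, electrolytes and coagulation profiles, will be carried out at enrolment, 48 hours later, day 5 or 6 of illness", and again at the follow-up visit. ALT belongs here.
- Daily plasma samples to day 6, which "will be assessed for viraemia levels, NS1 levels, and concentrations of various pro- and anti-inflammatory cytokines".

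CK is in none of the three. Elsewhere it appears only as an entry limit ("creatine kinase levels greater than 1000 U/l", Inclusion and exclusion criteria) and in the endpoint itself.

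On timing, Aims of the trial has treatment start on illness day 2 or 3 and "continue to the seventh or eighth day of illness". The Design section keeps patients under laboratory follow-up to study day 6 and sees them again on day 28. Under Statistical analysis, comparisons of laboratory markers are adjusted for the pre-dose value and the illness day at enrolment.

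**The concern.** The endpoint window and the sampling schedule do not match. A peak over six illness days needs samples that reach the end of the window, but the last scheduled in-window ALT falls on illness day 5 or 6. The uncovered days are the last days of treatment or those just after it, when cumulative exposure is greatest.

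The window is also fixed by illness day and not by first dose. For someone enrolled on day 3, it therefore includes a value that treatment cannot have affected.

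ALT and CK matter here because the Statins section says of this drug class: "The most common adverse effects are rises in the level of liver transaminases and myopathy". The trial's main purpose is safety, and these two peaks are its pre-specified laboratory measures of those two effects. A thinly sampled or diluted peak makes a finding of no difference less reassuring than it looks.

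**Working it through.** **Inputs.** Start on illness day e = 2 or 3, with the end of treatment on day 7 or 8 (Aims of the trial). Liver tests at e, e + 2 and illness day 5 or 6, then day 28 (Laboratory evaluation; Design). Window: days 3 to 8 (Secondary endpoints). Once-daily dosing for 5 days (Treatment and drug dispensation). Six doses per bottle (Randomization procedure).

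**The article's own end of treatment.** Five elapsed days give e + 5: 2 + 5 = 7 and 3 + 5 = 8, as stated. Six daily doses from day e also end on e + 5. Five daily doses end on e + 4, that is day 6 or 7.

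**Scheduled ALT by start day and late draw.**

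| Start day | Late draw | ALT days before follow-up | In window | Post-dose in window | Days from last ALT to e + 5 | Days from last ALT to e + 4 |
|---|---|---|---|---|---|---|
| 2 | 5 | 2, 4, 5 | 4, 5 | 2 | 7 − 5 = 2 | 6 − 5 = 1 |
| 2 | 6 | 2, 4, 6 | 4, 6 | 2 | 7 − 6 = 1 | 6 − 6 = 0 |
| 3 | 5 | 3, 5 | 3, 5 | 1 | 8 − 5 = 3 | 7 − 5 = 2 |
| 3 | 6 | 3, 5, 6 | 3, 5, 6 | 2 | 8 − 6 = 2 | 7 − 6 = 1 |

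In the third row the 48-hour draw (3 + 2 = 5) also meets the day 5 or 6 requirement, so one draw serves for both. In every row days 7 and 8 are empty: 2 of 6 window days. The last in-window ALT comes 1 to 3 days before the stated end of treatment, or 0 to 2 days before the last of five daily doses.

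**Pre-dose value inside the window.** For e = 3, write Y0 for the day-3 pre-dose value and Y1 for the highest post-dose value. The outcome is max(Y0, Y1). If treatment raises Y1 by δ, the outcome rises by max(Y0, Y1 + δ) − max(Y0, Y1), which lies between 0 and δ. It equals δ only when Y1 is already at least Y0, and it is 0 when Y1 + δ does not exceed Y0. The treatment difference can shrink but cannot grow. Y0 is also the covariate, so for some patients outcome and covariate are the same number. For e = 2 this does not arise, because the pre-dose value precedes the window.

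**CK.** Listed values after screening: none. A screening CK taken on illness day 3 does fall in the window, but it is pre-dose.

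**Whether existing blood reaches days 7–8.** If enrolment is study day 1, study day 6 is e + 5, that is illness day 7 or 8. If enrolment is study day 0, it is e + 6, that is illness day 8 or 9. The article does not state which numbering applies.

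**The case against.** A reader might infer that these endpoints cannot be obtained at all. For ALT the text does not support that: the endpoint is the highest value recorded in the window, and every patient started on day 2 or 3 has at least one scheduled post-dose value there.

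A reader might also conclude that CK is never measured after screening. That would rest on the silence of a condensed article. CK is an entry criterion and a named endpoint, and laboratory markers are to be adjusted for their pre-dose value, so testing is evidently intended. The full protocol may schedule it. What stands is that the article's itemised list omits a test its own endpoint needs.

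A third tempting reading is that half the values entering the maximum are pre-dose. That is true only for a day-3 enrolment with the late draw on day 5. With a day-6 draw it is one in three, and for day-2 enrolments it is zero. The article gives no distribution of enrolment day, so the frequency of each case is unknown.

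It is also fair to say that both arms share the same schedule and window, so the overlap creates no imbalance between them. The primary endpoint is adverse event rates compared by Fisher's exact test, not peak ALT or CK. These points limit the harm to attenuation and poor coverage in two secondary endpoints. They do not remove the mismatch over days 7–8 or the pre-dose overlap, both of which follow from stated text.

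**Conclusion.** The point holds in a limited form. As listed, the schedule leaves 2 of the 6 window days without ALT in every patient and yields one or two post-dose ALT values per patient. For day-3 enrolees it lets a pre-dose value be the peak. Peak ALT remains computable, but it is sparse and may miss a late rise. The size of the attenuation cannot be given, because it depends on the share of day-3 enrolments and on how often the pre-dose value is the highest. Neither is in the document.

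The CK part is conditional: the article lists no CK after screening, and the full protocol should be checked.

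The counts assume treatment starts on illness day 2 or 3, as the article says, and that only scheduled draws are used. Unscheduled tests could add values, but those would depend on who was tested. The matter deserves correction because these are the laboratory safety measures of a safety trial, but it does not affect the primary comparison.

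Separately, the 5 days of dosing and the six doses per bottle must be reconciled, since the length of the uncovered interval depends on them.

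**What to change.** Reconcile the Secondary endpoints and Laboratory evaluation sections as follows:

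1. Assay ALT and CK on the study-day-6 blood already being drawn. State how study days are numbered. If enrolment is day 0, so that study day 6 falls on illness day 9 for a day-3 enrolee, use the daily draw on illness day 8 for that patient.
2. Confirm that CK is measured at the existing 48-hour and illness day 5 or 6 draws, or add it there.
3. Define maximum ALT and maximum CK over in-window samples taken after the first dose, and use the pre-dose value only as the covariate.
4. Reconcile the treatment duration with the number of doses per bottle.

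The other endpoints defined over illness days 3 to 8 need no change on this account. The cost is a few extra assays per patient and a short amendment to the schedule and endpoint wording. No extra visit or blood draw is needed, provided the volume of the daily samples suffices.

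If recruitment is too far on to add assays, item 3 can still be adopted before unblinding. The report should then say that scheduled ALT ended on illness day 5 or 6 until follow-up.

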### Randomization procedure

Randomization to either treatment arm will be in a 1:1 ratio. Randomization will be stratified according to the ward of recruitment. A randomization list will be prepared and maintained confidentially from study staff by the clinical trials pharmacist. Block randomization using variable block sizes will be used.

A chronological log of all enrolled patients will be maintained. Each enrolled patient will be assigned the next available sequential study code. The assigned number will correspond to a coded, sealed, pre-packaged bottle containing six doses of either lovastatin or visually matched placebo. Blinding will be maintained amongst the attending physicians and nurses by ensuring that the study drug and the placebo have an identical appearance. In addition the administration schedule will be identical.

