### Safety reviews

This trial will be conducted in two phases with an escalation of dose if the results of an interim data review show no safety concerns within the first cohort treated with the lower dose. The dose will begin at 40 mg per day in cohort 1 and may continue at 80 mg per day in cohort 2. A DSMB (data and safety monitoring board) review will take place when day 6 study data are available from the 30th patient enrolled in cohort 1. If this review is satisfactory, the dose will be increased to 80 mg per day and recruitment into cohort 2 will commence. Further DSMB reviews will take place when day 6 study data are available from the 30th and 100th patients enrolled in cohort 2.

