### Treatment and drug dispensation

Patients will be assigned to one of two treatment arms:

Active medicinal product: 40 mg (stage 1) or 80 mg (stage 2) lovastatin once daily for 5 days.

Placebo: visually matched placebo once daily for 5 days.

The first dose will be given as soon as practically possible after enrolment.

An unblinded study pharmacist will prepare study drug bottles centrally and will distribute the bottles as required. Drugs will be stored in accordance with the manufacturers’ recommendations in a secure area. Lovastatin and the placebo must be maintained below 25°C. All movements of study medication will be recorded. Both individual subject and overall drug accountability records will be kept up to date by the study staff.

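### No liver test is scheduled between illness day 6 and the day 28 visit, although treatment is said to run to illness day 7 or 8 and maximum ALT is defined to illness day 8

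*Protocol article*

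**What the plan says.** All references are to the protocol article.

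- **Liver tests (Laboratory evaluation).** Renal, liver, electrolyte and coagulation tests "will be carried out at enrolment, 48 hours later, day 5 or 6 of illness and at the follow-up visit". The Design section puts the follow-up visit on day 28.
- **Daily tests (Laboratory evaluation).** "Haematocrit, platelet and total cholesterol measurements will be carried out daily or more frequently if clinically indicated". ALT is not in that list. Plasma is also taken daily to day 6, including after discharge, but for viraemia, NS1 and cytokines.
- **Endpoint (Secondary endpoints).** "maximum alanine transaminase (ALT) and creatine kinase (CK) recorded between day 3 and 8 of illness".
- **Length of the course.** The Aims section says: "Our proposed treatment course will start on the second or third day of illness and continue to the seventh or eighth day of illness". Treatment and drug dispensation gives "40 mg (stage 1) or 80 mg (stage 2) lovastatin once daily for 5 days". The Randomization procedure describes a "pre-packaged bottle containing six doses of either lovastatin or visually matched placebo".
- **Safety reviews.** The review that decides on dose escalation takes place "when day 6 study data are available from the 30th patient enrolled in cohort 1". Cohort 2 has further reviews on the same day 6 basis, at its 30th and 100th patients.
- **Why ALT matters here.** The Background section on statins lists raised transaminases among the most common adverse effects and describes these effects as rare and apparently dose-related. The primary endpoint is safety and tolerability.

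**The concern.** The late liver test is tied to the day of illness, not to the number of doses taken. The later a patient enters, the less of the course lies behind the last scheduled ALT. The endpoint window and the stated course both extend past that test, so the maximum is taken over a period whose final days have no routine measurement.

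Both arms are sampled in the same way, so the comparison is not tilted towards either. But if a drug effect on ALT builds over the course, or shows just after it, the schedule would understate it. In a trial about safety, that error points towards reassurance. Laboratory evaluation also notes that dengue itself may disturb liver function, so a randomised comparison late in the course is the natural way to separate drug from disease. An analysis plan cannot recover a sample that was never assayed.

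**Working it through.** This is day arithmetic on the protocol's own schedule.

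**Inputs.** Start of treatment on illness day s = 2 or 3 (Aims). Number of once-daily doses n = 5 (Treatment and drug dispensation) or 6 (bottle contents, Randomization procedure). Third liver test on illness day d = 5 or 6 (Laboratory evaluation). Endpoint window: illness days 3 to 8 (Secondary endpoints).

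**Step 1: reproduce the stated course end.** Last dose day = s + n − 1.
- n = 6: 2 + 5 = 7 and 3 + 5 = 8. This matches the Aims section.
- n = 5: 2 + 4 = 6 and 3 + 4 = 7. As last-dose days these are one day earlier than the Aims section, although five full days elapsed from the first dose would also end on day 7 or 8.

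The three statements on course length therefore do not plainly agree, and the gap has to be shown on both readings.

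**Step 2: last scheduled ALT before day 28.** This is the later of s + 2 (the 48-hour test) and d.
- s = 2: 48-hour test on day 4, so the last ALT is on day 5 or 6.
- s = 3: 48-hour test on day 5, so the last ALT is on day 5 or 6. If d = 5, the two tests fall on the same day.

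**Step 3: gap = end of dosing − last scheduled ALT.** A dose given on the day of the draw counts as already taken; if blood is drawn first, one more dose follows it.

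| Start | Last ALT | Gap, five doses | Gap to course end in Aims (same as six doses) |
|---|---|---|---|
| day 2 | day 5 | 6 − 5 = 1 | 7 − 5 = 2 |
| day 2 | day 6 | 6 − 6 = 0 | 7 − 6 = 1 |
| day 3 | day 5 | 7 − 5 = 2 | 8 − 5 = 3 |
| day 3 | day 6 | 7 − 6 = 1 | 8 − 6 = 2 |

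**Step 4: coverage of the endpoint window.** The window has six days (3 to 8). With the third test on day 6, days 7 and 8 have no scheduled ALT (2 of 6). With it on day 5, days 6, 7 and 8 have none (3 of 6).

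**Step 5: the coinciding draw.** For s = 3 and d = 5, a single sample on day 5 can satisfy both schedule entries. Doses fall on days 3, 4 and 5, so it follows two or three doses, depending on whether blood is taken before that day's dose. It is then the only scheduled post-dose ALT in the window.

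**Step 6: where a study day 6 sample would fall.** The article does not say whether enrolment is study day 0 or 1. If it is day 1, study day 6 is illness day s + 5 = 7 or 8: the day after the last of five doses, or the day of the sixth. If it is day 0, study day 6 is illness day s + 6 = 8 or 9, and day 9 lies one day beyond the endpoint window.

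**The case against.** A reader might infer that liver toxicity at the end of the course is never measured. The documents do not support that:

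- Liver tests are repeated at day 28, so a rise that persists would be seen.
- With five daily doses, a patient who starts on day 2 and is tested on day 6 is sampled on the last-dose day. A start on illness day 1, which eligibility allows although the Aims section does not foresee it, leaves no gap with five doses (last dose on day 5, last ALT on day 5 or 6).
- The endpoint takes the maximum recorded value, so ALTs ordered by ward doctors inside the window would count.
- Adverse events are recorded throughout, with contact to study day 6 and a visit at day 28. Clinically apparent liver injury would be counted.

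These points stand, and they narrow the concern to a transient, silent rise. They do not remove it. Clinically ordered tests are selective, and patients may be outpatients from study day 3. Day 28 lies outside the endpoint window and after the day 6 data that trigger each review.

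It can also be said that a common window of days 3 to 8, shared with platelets, haematocrit and oxygen saturation, only bounds which values count and does not promise an ALT on each day. That is fair: this is a weak match between schedule and endpoint, not a formal contradiction. Likewise the coinciding draw is a possibility, since a site can use the day 6 option.

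The DSMB section lists adverse events, disease progression and viraemia curves for the report, but no ALT table. So it cannot be claimed that the board would otherwise have seen a late ALT, only that none would be routinely available to it in the day 6 data.

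Finally, the article may condense a fuller laboratory schedule. CK belongs to the same endpoint and has no timing there at all. But for liver tests the article gives an explicit list of time points, and the point is raised against that list.

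It is also tempting to convert the gap into a loss of power. The protocol states no power for maximum ALT and nothing on how an ALT effect grows with doses, so any such figure would be invented.

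**Conclusion.** The point holds in limited form: the listed schedule has no liver test between illness day 6 and day 28, and so stops short of the course end given in the Aims section and of the last two or three days of the maximum-ALT window. The gap is small, from none to two doses on the five-dose reading and one to three days on the longer one. It is widest for patients who start on illness day 3.

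This rests on starts on illness day 2 or 3 as the Aims section says, on once-daily dosing, and on the listed time points being the full liver schedule. Maximum ALT is a secondary endpoint and the primary comparison is of adverse event rates. The matter is therefore a cheap improvement that should be made, not a defect that undermines the trial.

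**What to change.** 1. In Laboratory evaluation, schedule an ALT on study day 6 for every patient. State whether enrolment is study day 0 or 1.
2. Require the 48-hour and illness day 5 or 6 tests to be separate draws, so that one sample cannot serve as both.
3. In Secondary endpoints, count the study day 6 value in maximum ALT explicitly, so that it is kept even if it falls on illness day 9.
4. Include the study day 6 ALT in the day 6 data prepared for each DSMB review.
5. Reconcile the Aims section, Treatment and drug dispensation, and the bottle contents in the Randomization procedure on the length of the course. Which of them is right is for the sponsor to state.

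**Cost.** About one extra ALT assay per patient, at a contact and on a blood draw already planned, plus a second for some day 3 starters whose two tests would have been one. For the 30 patients before the first review and 300 in cohort 2, that is about 330 assays, plus those for patients who join cohort 1 while the review is pending. No extra visit is needed. It has to be settled before recruitment, because the value may not be recoverable later.
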